### Outcome Measures

#### Overview

We will measure primary and secondary outcomes. Primary outcomes are based on the intertwined process cognitive-affective model, as described by Dillard and Shen [5] and Zhang [32] (Figure 2). In this model, there are two antecedents to reactance: the strength of the threat to freedom and trait proneness to reactance. Reactance is conceptualized as a mediator between the antecedents of reactance and behavioral intent to promote health-related activities. It is an intertwined process consisting of a cognitive and affective component that can be an experience of hostile, aggressive, or angry feelings. Furthermore, attitudinal and behavioral intentions are the consequences of reactance. The assessment of behavioral intentions can also help measure the direct restoration of freedom, which involves performing forbidden behavior and restoring participants’ need for self-determination and control [33]. In addition, source appraisal, which refers to the perception of the message source, is another important outcome of reactance [34].

**Figure 2 figure2:**
[figure not shown]
An intertwined process cognitive-affective model as described in Dillard and Shen with the addition of source appraisal from Zhang.

#### Primary Outcome Measures

##### Trait Reactance Proneness

Trait reactance refers to reactance being a personal trait that causes some people to be more or less prone to experiencing reactance [35]. This implies that individuals tend to differ in their ways of perceiving and reacting to situations when their freedom is threatened, depending on their personalities. The propensity to trait reactance in this study will be measured using the Hong Psychological Reactance Scale developed by Hong et al [35]. The scale consists of 11 items that comprise 4 major factors: emotional response to restricted choice, reactance to compliance, resistance to influence from others, and reactance to advice and recommendations [35] (Textbox 1). These items are measured on a 5-point Likert scale with the following points: (1) strongly disagree, (2) disagree, (3) neither agree nor disagree, (4) agree, and (5) strongly agree [35].

Trait reactance items based on the Hong Psychological Reactance Scale.
**Emotional Response to Restricted Choice**
I become frustrated when I am unable to make free and independent decisions.It irritates me when someone points out things that are obvious to me.I become angry when my freedom of choice is restricted.
**Reactance to Compliance**
Regulations trigger a sense of resistance in me.I find contradicting others stimulating.When something is prohibited, I usually think, “That’s exactly what I am going to do.”
**Resistance to Influence From Others**
I resist the attempts of others to influence me.It makes me angry when another person is held up as a role model for me to follow.When someone forces me to do something, I feel like doing the opposite.
**Reactance to Advice and Recommendations**
I consider advice from others to be an intrusion.Advice and recommendations usually induce me to do just the opposite.

##### Threat to Freedom

To measure the threat level of the message, we will use the following 4 items from Dillard and Shen [5], each measured using a 5-point Likert scale:

The message threatened my freedom to choose.The message tried to make a decision for me.The message tried to manipulate me.The message tried to pressure me.

##### Psychological Reactance

Following Dillard and Shen’s model, psychological reactance is assessed by measuring anger and negative cognition. Therefore, the average of all items on anger and negative cognition is an indicator of reactance. To measure anger, we will use a 5-point scale for the following 4 affirmations [5]:

This message makes me feel irritated.This message makes me feel annoyed.This message makes me feel aggravated.This message makes me feel angry.

Negative cognition will be measured using the Likert scale from Quick et al [36-38] instead of the thought-listing procedure used by Dillard and Shen [5] because of the large sample size in this study. In a recent comparison of 3 methods for measuring negative cognition [39], the Likert scale was reported to have several advantages, including measurement economy as well as the flexibility to use these measures outside of the laboratory and when examining multiple candidate messages. The following 3 items, each measured on a 5-point Likert scale, will be used to measure negative cognition:

The thoughts I had while watching this video were mostly unfavorable.The thoughts I had while watching this video were mostly negative.The thoughts I had while watching this video were mostly bad.

##### Source Appraisal

Source appraisal will be assessed using the question, “The narrator of this video was...” and 7 semantic differential items anchored on either end with opposing adjectives: stupid or smart, unknowledgeable or knowledgeable, uninformed or informed, unintelligent or intelligent, unqualified or qualified, unreliable or reliable, and inexpert or expert [40]. The category ratings will be scored from 1 to 5, and higher scores will imply more unfavorable evaluations of the message source.

##### Attitude

Attitude toward message advocacy will be measured using four 5-point Likert items from Shen [41]:

I agree with what the message recommends.I support what the message advocates.I am in favor of the position in the message.I endorse the claims made in the message.

Data from trait reactance proneness, threat to freedom, psychological reactance, source appraisal, and attitude will be used to assess objective 1.

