**Methods:**

This is a parallel group, randomized controlled trial comparing an intervention video narrated by a low, equivalent, or high social authority against a content placebo video and a placebo video. Using a web-based recruitment platform, we plan to enroll 4000 participants aged between 18 and 59 years who speak English and reside in the United Kingdom. The primary end points will include measures of the antecedents to reactance (proneness to reactance and threat level of the message), its components (anger and negative cognition), and attitudinal and behavioral intent toward sugar intake. We will measure behavioral intent using list experiments. Participants randomized to the placebo videos will be given a choice to watch one of the sugar-intervention videos at the end of the study to assess participant engagement with the entertainment-education video.

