## Methods

### Trial Design

This study consists of a parallel group RCT. Participants will be randomized to 1 of 5 arms: either the same sugar-intervention video narrated by a preadolescent daughter (arm 1: low social authority), the daughter’s mother (arm 2: equivalent social authority), or a family physician (arm 3: high social authority), or a content placebo video with a health message about tanning and sunscreen (arm 4: no sugar message), or a placebo video about earthquakes (arm 5: no sugar or health message). We will randomize the participants in a 1:1:1:1:1 ratio to the trial arms. Participants will watch 1 video once from start to finish.

Nested in each of the five trial arms is a list experiment. For each list experiment, participants will be randomized at a 1:1 ratio to a control or treatment group. The control group will receive a list of 5 items about behavioral intent (unrelated to sugar consumption). The treatment group will receive the same 5 items and a sensitive item about behavioral intent to reduce sugar intake. We will use the list experiment to reduce social desirability bias, as participants may already be primed to answer favorably to questions about sugar consumption.

At the end of the study, participants assigned to the content placebo (*arm 4*) or placebo (*arm 5*) will be given a choice to watch the video intervention. Their choices will be recorded. Participants who choose to watch will be randomized at a 1:1:1 ratio to the sugar video narrated by the daughter, mother, or physician. The complete trial flowchart is presented in Figure 1.

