#### Explanation for the Choice of Comparators

We will compare the 3 intervention videos (*arms 1-3*) with each other (pairwise) to determine which social authority status is associated with the largest change in reactance and behavioral intent to reduce the intake of added sugars. In addition, we will compare the 3 intervention videos with the content placebo video (*arm 4*) and the placebo video (*arm 5*).

The content of the placebo video is similar in style to the sugar video. It is also animated, with a duration of 3.42 minutes, and has a health message about tanning and using sunscreen [30]. We used the content placebo video to isolate the *content effect* of the sugar-intervention video. It is possible that any video with a health message (eg, sunscreen protection) can improve overall health awareness and thus increase behavioral intent to reduce sugar intake. As both the intervention and content placebo videos have a health message, we expect that a significant difference in behavioral intent between the 2 videos (after random assignment) can be attributed to the content of the sugar message.

We will also compare each sugar-intervention video with a placebo video. The placebo describes the causes and characteristics of earthquakes [31] and contains no health-related or sugar consumption content. A significant difference in behavioral intent to reduce sugar intake between the content placebo and placebo videos (after random assignment) can therefore be attributed to the content of the sunscreen message. We call this difference the *health awareness effect*. We describe the *total intervention effect* as the difference between the sugar-intervention and the placebo videos, which is the sum of the content and health awareness effects.

We will also implement a list experiment in each arm with the control list as the comparator. The control list will include 5 items about general behavioral intent. The treatment list will include the same 5 control items plus a sixth item about behavioral intent toward reducing sugar intake. The control list (comparator) is needed to measure the prevalence of behavioral intent to reduce sugar intake, described in the *Behavioral Intent* section.

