### Statistical Methods

#### Statistical Methods for Primary and Secondary Outcomes

For the descriptive statistics, we will obtain means and SDs of age, sex, country of residence, and education status variables. We will use an analysis of variance to estimate pairwise differences in means between the sugar-intervention videos, content placebo video, and placebo video. We will use the Tukey range method to create confidence intervals for all pairwise differences between the means while controlling for the family error rate. Within each trial arm, we will estimate the prevalence of behavioral intent as the difference between the treatment and control list for each list experiment. From these estimates, we will obtain the differences in means between trial arms. This approach is analogous to a difference-in-difference analysis, which we will implement by specifying the main and interaction terms in an ordinary least squares (OLS) regression model. The OLS equation for each list experiment is given as follows:

y = b_0_ + b_1_*VideoArm* + b_2_*TreatList* + b_3_*VideoArm* × *TreatList*

where y is the number of statements in the list that the participant agreed with, *VideoArm* indicates the arm to which the participant was assigned, and *TreatList* indicates if the participant was assigned to the treatment list within that arm. We will calculate standard errors, 95% CIs, and *P* values for linear combinations of coefficients from the OLS model. We will use R statistical software to perform the analysis.

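### The attitude items ask about whichever message was shown, so the 7 of 10 attitude contrasts that involve a placebo video cannot be read as effects on attitude to sugar

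*Protocol article*

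**What the plan says.** The abstract (Methods) lists among the primary end points "attitudinal and behavioral intent toward sugar intake". The Attitude section, under Primary Outcome Measures, defines the construct more narrowly: "Attitude toward message advocacy will be measured using four 5-point Likert items". The first item reads "I agree with what the message recommends". The other three ask about what the message advocates, its position and its claims. None mentions sugar. The section assigns the attitude data to objective 1, the effect of the narrator's social authority.

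The messages differ by arm. Arms 1-3 see the same sugar video with different narrators. Under Trial Design, the two comparators are "a content placebo video with a health message about tanning and sunscreen (arm 4: no sugar message") and "a placebo video about earthquakes (arm 5: no sugar or health message"). The comparator section says that the earthquake video "contains no health-related or sugar consumption content".

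On the analysis, the comparator section states, beyond the comparisons among the three narrators, that "we will compare the 3 intervention videos with the content placebo video" and with the placebo video. Statistical Methods plans an analysis of variance for "pairwise differences in means between the sugar-intervention videos, content placebo video, and placebo video", with Tukey intervals for every pair. Neither section exempts attitude.

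**The concern.** A contrast between arms has meaning when the same quantity is measured in both. Here the object of the rating changes with the arm. Randomization makes the participants comparable, but it cannot make an answer about sunscreen comparable with an answer about sugar.

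The gap matters because the end point is primary, its label in the abstract names sugar, and the analysis as written produces attitude contrasts against both placebo videos. A significant difference on that scale could be reported as the video changing attitudes to sugar, in either direction, when it may only reflect that people rate two pieces of advice differently, or give neutral answers when no advice was offered.

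**Working it through.** The plan states no figure for attitude, so there is none to reproduce. The check compares the sections first and then illustrates the size.

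**1. What the attitude score refers to in each arm**

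| Arm | Video | Object of the four items |
|---|---|---|
| 1-3 | Sugar reduction (daughter, mother, physician) | Reducing added sugar |
| 4 | Tanning and sunscreen | Sunscreen advice |
| 5 | Causes and characteristics of earthquakes | No evident recommendation |

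The entry for arm 5 is inferred from the description of the video.

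**2. Contrasts affected**

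- All pairs of five arms: 5 × 4 / 2 = 10.
- Pairs within arms 1-3: 3 × 2 / 2 = 3. These share one message and are interpretable.
- Pairs that involve arm 4 or 5: 10 − 3 = 7. Six set a sugar video against a placebo video and one sets arm 4 against arm 5. None measures a difference in attitude to sugar.

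**3. How easily a change of object would reach significance**

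Inputs: n = 4000 / 5 = 800 per arm (Sample Size; 1:1:1:1:1 allocation). The document gives no SD for attitude, so 0.85 to 1.0 on the 1-5 scale is an assumption. Attitude to sugar is taken as equal in all arms.

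- SE of a difference = SD × √(2/800) = 0.0425 (SD 0.85) or 0.050 (SD 1.0).
- Tukey critical value for five groups, 5% familywise: about 2.729.
- Probability of significance ≈ 1 − Φ(2.729 − gap/SE).

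| Gap due only to the object | SD 0.85 | SD 1.0 |
|---|---|---|
| 0.1 | 0.35 | 0.23 |
| 0.2 | 1 − Φ(2.729 − 4.706) = 0.98 | 1 − Φ(2.729 − 4.000) = 0.90 |
| 0.3 | 1.00 | 1.00 |

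Without the Tukey adjustment, the 0.2-point gap is significant with probability 0.98 (SD 1.0) to 1.00 (SD 0.85). The table does not show that such a gap exists, only that a trial of this size would flag a small one.

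**4. Cost to the valid contrasts**

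The three-group Tukey critical value is about 2.345 (2,397 degrees of freedom). The ratio 2.729 / 2.345 = 1.16, so carrying the seven other contrasts makes the narrator intervals on attitude about 16% wider. At SD 1.0 the half-width is 2.729 × 0.050 = 0.136 instead of 2.345 × 0.050 = 0.117.

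**The case against.** The strongest reply is that the protocol does not promise what these contrasts fail to deliver.

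- The operative definition in the Methods concerns agreement with the message's advocacy, and the items match it. The abstract's wording is shorthand.
- Attitude is assigned to objective 1, and the null hypothesis names only the three narrators. That comparison is sound as planned.
- The content, health awareness and total intervention effects are written out for behavioral intent (comparator section) and for mean state reactance (Strengths and Limitations), never for attitude.
- The list experiments ask about sugar in every arm, so an effect on intent versus placebo can still be estimated.
- The ANOVA sentence names no outcome, and the assessment schedule (Figure 3) is not available here, so it cannot be confirmed that arms 4 and 5 receive the attitude items.

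All of this stands, and it limits the point. A reader might infer that the attitude end point does not exist in two arms, or that the trial fails on attitude altogether. The documents do not support that: the construct as the Methods define it is measured wherever a message advocates something, and objective 1 is intact. Nor do they support a prediction that sunscreen advice would score higher or lower than sugar advice, since no expected attitude means are given.

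The reply does not remove the gap between sections. The abstract names sugar as the object, two sections plan five-arm comparisons, and nothing exempts attitude or says how a placebo contrast on it should be read. The argument in Strengths and Limitations that the earthquake video supplies a baseline is made for state reactance, where a video that threatens no freedom should score near the floor. Agreement with a recommendation that was never made has no such natural baseline.

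**Conclusion.** The point holds in a limited form. Followed as written, the plan yields 7 of 10 attitude contrasts that cannot be read as effects on attitude to sugar. The other 3, among the narrators, are valid, and so is the list-experiment comparison of intent across all five arms. The consequence is a risk of misreading a primary outcome, not a loss of any stated objective.

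The conclusion rests on the item wording and the video descriptions. It assumes that the attitude items are asked in all five arms, which the text nowhere denies, and that the earthquake video recommends nothing, which its description implies. The significance probabilities also rest on the assumed SDs and gaps and are illustrative.

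**What to change.** Add to Statistical Methods that the attitude ANOVA and Tukey contrasts are restricted to arms 1-3, with the three-group critical value (about 2.345 instead of 2.729). State that effects on attitude to sugar versus either placebo video are not estimable. Change the abstract's label so that it describes agreement with what the message advocates, as the Attitude section does.

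The cost is a few sentences. The placebo contrasts on attitude are given up, or shown as description only and labeled as ratings of different messages. In return, the narrator intervals on attitude become narrower.

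Rewording the items around sugar is not a remedy here. The Results section reports that data collection ended in December 2020, and direct sugar questions could have cued participants in arms 4 and 5 if asked before the list experiments. That section also reports the analysis as completed in April 2021, so the restriction now applies to how the attitude results are analyzed for publication and interpreted. It should be described there as a clarification made after the protocol.

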### Objective

In a web-based entertainment-education video setting, there is limited, high-quality experimental evidence on the relationship between reactance and the perceived social authority of a message agent. Using a randomized controlled trial (RCT), we will evaluate the effect of social authority status on reactance to a short animated video on the intake of added sugars. The sugar message will be narrated by either (1) a preadolescent daughter, who has low authority status relative to the other narrators, (2) the daughter’s mother, who has equivalent social authority to the target audience, or (3) the family physician, who is an expert with high social authority. Results from this study will facilitate the development of videos for reducing reactance and improve the persuasiveness of health messages in web-based settings.

This study aims to achieve the following objectives:

Determine the effect of the narrator’s social authority (daughter, daughter’s mother, or family physician) on reactance to a sugar reduction message.Establish the video’s effectiveness in improving behavioral intent to reduce the intake of added sugars.Quantify participants’ interest in watching a short animated video about reducing the intake of added sugars.

Our null hypothesis is that the social authority of the child, who has low perceived social authority, the mother, who has equivalent perceived social authority, or the family physician, who has high perceived social authority, will have no effect on reactance to a video about reducing sugar intake.

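### Trait reactance proneness is defined as a personality trait that precedes reactance, yet it is listed as a primary outcome and used to assess the narrator's effect

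*Protocol article*

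**What the plan says.** The Abstract (Methods) states that "The primary end points will include measures of the antecedents to reactance" and names proneness as one of them. The description of the Hong scale stands under the heading Primary Outcome Measures. The closing sentence of the Attitude section groups the trait with four scales that ask about the message, the narrator or the viewer's response: "Data from trait reactance proneness, threat to freedom, psychological reactance, source appraisal, and attitude will be used to assess objective 1". Objective 1 is to "Determine the effect of the narrator’s social authority (daughter, daughter’s mother, or family physician) on reactance to a sugar reduction message".

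The article's own model gives the trait a different place. The Overview of outcome measures says that "there are two antecedents to reactance: the strength of the threat to freedom and trait proneness to reactance" and that "Reactance is conceptualized as a mediator between the antecedents of reactance and behavioral intent to promote health-related activities". The Trait Reactance Proneness section adds: "Trait reactance refers to reactance being a personal trait that causes some people to be more or less prone to experiencing reactance". It attributes the differences to the person: "individuals tend to differ in their ways of perceiving and reacting to situations when their freedom is threatened, depending on their personalities".

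The section Statistical Methods for Primary and Secondary Outcomes gives one method for comparing arm means, an ANOVA with Tukey intervals. It gives a regression for the list experiments with arm, list type and their interaction. Neither contains the trait or any other covariate. The trait is also not among the variables to be described (age, sex, country and education).

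**The concern.** A primary outcome should be something the randomised exposure could change. By the article's definitions, trait proneness exists before the video and influences how the viewer responds to it. A difference between arms in trait scores would most likely be chance imbalance, yet objective 1 places those scores beside the real response measures.

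Two things are at stake. First, one declared primary outcome cannot answer its objective and adds an opportunity for a false positive. Strengths and Limitations argues that, because of randomisation, arm differences in reactance toward the message should reflect the narrator. Applied to the trait, that argument would turn imbalance into an effect. Second, a characteristic that is already collected and is expected to predict state reactance is given no role in which it could sharpen the comparisons of interest.

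**Working it through.** The main point needs no arithmetic, and the plan gives no figure for it. The sample-size calculation is built on list counts and does not enter here.

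**1. Can the scale carry a narrator effect?**
- *Trait items:* all 11 concern general disposition, such as frustration at restricted choice, response to regulations and response to advice. None refers to the video, message or narrator.
- *Threat to freedom:* this is also called an antecedent, but its four items ask what the message did. It is a legitimate post-video outcome, and the point does not extend to it.
- *Anger, negative cognition, source appraisal and attitude:* all ask about the message, the video or the narrator.

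Only the trait scale is out of place in objective 1.

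**2. Chance of a spurious arm difference on the trait.** Assume the video leaves trait scores unchanged. With five arms of 4000/5 = 800, error degrees of freedom are 4000 − 5 = 3995. A Tukey family at 5% should then show at least one significant pair in 5% of trials. A simulation of 20,000 null trials gave 5.1%.

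**3. Contribution to error across objective 1.** Tukey controls error over arm pairs within one outcome, and no control across outcomes is stated. If the scales were independent, with each family at 5%:
- five outcomes: 1 − 0.95^5 = 22.6%
- four outcomes, trait removed: 1 − 0.95^4 = 18.5%

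Independence is for illustration, since the scales are likely to be correlated.

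**4. Possible gain as a covariate.** Let r be the correlation of trait with state reactance. The article does not give r, so 0.2 to 0.5 is an assumed range. Adjustment multiplies residual variance by 1 − r². The standard error of an arm difference, in SD units, is √(2/800 × (1 − r²)), which is 0.050 at r = 0. The Tukey critical value on the t scale is 2.729, and z for 80% power is 0.842. The detectable difference is (2.729 + 0.842) × SE. Power is shown for an illustrative true difference of 0.15 SD, as Φ(0.15/SE − 2.729).

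| r | Fall in residual variance | Detectable difference (SD) | Power at 0.15 SD |
|---|---|---|---|
| 0 | 0% | 0.179 | 60.7% |
| 0.2 | 4% | 0.175 | 63.0% |
| 0.3 | 9% | 0.170 | 66.1% |
| 0.4 | 16% | 0.164 | 70.7% |
| 0.5 | 25% | 0.155 | 76.9% |

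**5. Timing.** The gain in step 4 is clean only if the scale was asked before the video. Participant Timeline mentions the video before the survey questions, but the text does not place the trait scale, and the schedule figure is not shown here.

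**The case against.** The strongest reply is that the article never says trait scores will be compared across arms. The ANOVA sentence names the videos but no scale, and being used to assess objective 1 could cover use as an antecedent. This stands in part. That the trait is tested is an inference from its primary-outcome label and from a methods section written for primary and secondary outcomes. The label itself is explicit, however, and no other use is stated.

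A reader might go further and infer that a chance trait difference would be counted as a narrator effect. The documents do not support that. There is no rule that counts significant scales. Psychological Reactance defines the reactance indicator from the anger and negative cognition items, and Strengths and Limitations expresses its effects in mean state reactance. Most of the error in step 3 of the working is a general matter of several primary outcomes.

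A reader might also treat the unadjusted models as a defect in themselves. They are not: under randomisation they are unbiased, and an unseen analysis plan may list covariates. Nor is the lack of a trait-by-narrator interaction an error, because none of the three objectives asks about effect modification.

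**Conclusion.** The point holds in a limited form. Trait proneness is misclassified: by the article's own definitions it cannot measure the narrator's effect, yet it is a declared primary outcome assigned to objective 1. Read with the only stated analysis, this implies about a 5% chance of a spurious arm difference on that scale. That figure assumes the video does not alter answers to the trait items. If the scale followed the video and answers shifted, the difference would be carry-over into a disposition measure, which is still not reactance to the message.

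The estimates for state reactance, threat, source appraisal and attitude remain valid. The loss of precision is conditional: it depends on an unstated correlation and on when the scale was asked. At r = 0.2 the gain is slight, and at r = 0.5 it is worthwhile.

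**What to change.** Remove trait proneness from the primary outcomes in the Abstract and in Primary Outcome Measures, and from the objective 1 sentence. Report it by arm as a participant characteristic, and do not count arm differences in it as evidence for objective 1. State when the scale was asked relative to the video.

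- **If asked before the video:** include the trait score, with age, sex and education, as covariates in the models for threat, state reactance, source appraisal and attitude.
- **If asked after the video:** keep the model without the trait as primary. Age, sex and education may still be adjusted for. Give the trait-adjusted model as a sensitivity analysis.

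Do not choose between these by testing whether trait means are equal across arms, because a non-significant result would not show that the video left the answers unaffected. A trait-by-narrator interaction is optional and should be labelled exploratory. The article reports that analysis was completed in April 2021, so any covariate model not fixed beforehand should be labelled post hoc.

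The cost is small: no new data, one fewer primary outcome and a slightly longer model.
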